### Recruitment strategy

Involving managers is vital for a successful implementation of an organizational intervention in the home care sector [28]. Therefore, during the development phase of the project, representatives from the research group participated in three meetings with the unit leaders. To maximize the participation rate when assessing physical behavior and musculoskeletal pain, we visited each unit leader to present the intervention, aiming to generate a positive attitude toward the project, which would hopefully be transferred to the workers. During these visits, leaders also advised on the best implementation and recruitment strategies. In addition, to better inform the home care workers of the intervention and associated measurements, researchers will visit each unit and discuss these aspects with the home care workers, who will also receive flyers with short and concise information about the measurement procedures and the equipment involved. At the time of submission, participant recruitment is ongoing.

## Methods – assignment of interventions

### Randomization

A cluster randomized design will be used, since participants working together in the same unit are required to communicate and cooperate on certain assignments. The randomization procedure (1:1 ratio) will be carried out by a third party, i.e. the Unit for Applied Clinical Research at the Norwegian University of Science and Technology (https://www.ntnu.edu/mh/akf/randomisering). As the allocation of units to intervention or control arm will be concealed until all baseline measures have been completed, neither researchers nor participants will initially know to which arm they have been allocated. To ensure that a similar number of participants is assigned to the control and the intervention arm, the units will, during randomization, be stratified by their size (number of participants).

### Blinding

Due to the operations manager direct involvement in the intervention implementation after baseline, participant blinding will not be possible. Likewise, researcher blinding is unfeasible, as the researchers are involved in the delivery of the intervention.

## Methods – data collection, management and analysis

### Data collection methods

For an overview over assessment timeline see Table 1. Data will be collected at baseline before the intervention and again at the end of the intervention period. It is expected that the baseline measurements will be collected over a period of 6–8 weeks, but this phase may need to be extended if recruitment is slow. The intervention will thus commence once a sufficient number of participants is recruited and will continue until all post-intervention measurements have been completed. For the latter, 4 weeks are deemed sufficient, as all individuals will already be familiar with the procedures and no delays are anticipated. All collected data will be uploaded to a secure online storage system where it will be kept with access limited to the researchers conducting the study. All data will be pseudo-anonymized before analysis. In accordance with the regional ethical committee regulations, all data will be anonymized 5 years after the project is finalized, in 2028.

**Table 1 Tab1:**
[figure not shown]
Schedule for enrolment, intervention and assessment in accordance with the SPIRIT statement [29]

#### Musculoskeletal pain

During both baseline and post-intervention measurements, participants will provide a lower back and neck/shoulder pain score when leaving the workplace. They will be instructed to select the numerical value on a 0 (no pain at all) to 10 (strong pain) scale [27] that most closely matches the level of pain experienced during the shift. They will be guided by the corresponding questions: “How much pain did you have in the lower back at the end of the working day?” and “How much pain did you have in the shoulder/neck at the end of this working day?”

#### Physical behavior

Each home care worker will be equipped with three Axivity AX3 (3-Axis Logging Accelerometer; Axivity Ltd., Newcastle upon Tyne, UK) accelerometers. One sensor will be placed on the thigh, approximately 10 cm above the patella, one will be placed on the upper back, at the T1 − T2 height, and the last one will be placed on the upper arm just below the deltoideus muscle. During measurements, participants will fill out an activity diary, indicating when they woke up, when they started their work shift, when it ended, and when they went to bed.

The initiation and setup of the AX3 accelerometers will be conducted in the Axivity software OmGui. The accelerometers will be set to record at ±8 g, at a frequency of 25 Hz for seven uninterrupted days. At the end of the recording period, the data will be downloaded from the accelerometers using OmGui and the acceleration signal will be processed in the MATLAB software Acti4 [30]. In Acti4, the acceleration signal is processed into physical behaviors including lying, sitting, standing, walking and running. In addition, Acti4 also detects the extent of trunk inclination and arm elevation. Thus, postures can be assessed for each of the physical behaviors [31]. Periods of work, leisure and sleep will be determined using the information in the activity diary.

While at work, home care workers will digitally register, in the home care registry, the start and end times of all assignments, which allows physical behavior to be analyzed specifically while the home care worker cares for patients with different ADL scores.

#### Anthropometric measures and questionnaire

During baseline measurements all participating home care workers will have their height (using a SECA 206 wall mounted measuring tape) and weight (using a standard bodyweight scale) measured, and will complete a questionnaire containing questions on demographics, socioeconomic status, self-rated health, and musculoskeletal pain. To assess the workplace psychosocial demands of the home care workers, pertinent scales from the Copenhagen Psychosocial Questionnaire III (COPSOQ III) will be adopted [32]. The scales will be “quantitative demands”, “work pace”, “emotional demands”, “influence”, “quality of leadership”, and “social support” from colleagues, as well as “social capital” (as a combination of vertical trust, longitudinal trust and organizational justice) [33].

#### GoldiCare tool

At the start of the intervention, each operations manager in the intervention group will receive an email with a link to a secure cloud server containing the GoldiCare tool. During the entire intervention period, operations managers will use the GoldiCare tool and store all entered data in the cloud server, allowing the researchers to check inputs, monitor compliance and provide regular feedback. To obtain a baseline for subsequent comparisons, the operations managers will be instructed to use the GoldiCare tool to record information for the week preceding the intervention.

#### Process evaluation

At the end of the intervention, operations managers will be invited to partake in qualitative semi-structured interviews to assess their compliance with the GoldiCare intervention and obtain their general perceptions of it. The home care workers will be invited to share their opinions of the intervention as a part of focus group discussions. While the goal of the focus groups is to ascertain whether home care workers found the intervention beneficial with respect to their health and productivity, the operations manager interviews will focus on the GoldiCare tool, how easy it was to use and its value in terms of efficiency in scheduling. All interviews and focus groups will be recorded. Two researchers will be present at the focus groups discussions.

### Statistical methods

To evaluate the primary outcomes, lower back pain and shoulder/neck pain in the intervention and the control group will be compared after the 16-week intervention, applying the intention-to-treat principle [34]. When conducting analyses, special considerations will have to be taken due to the clustered trial design [35, 36]. We will therefore adjust analyses for the effects of clustering by using mixed-model methods to account for differences between clusters while still providing insight into changes at the individual level [37]. Mixed-models will also be used to account for repeated measurements of pain intensity and fatigue at the individual level both at baseline and post-intervention. Parametric or non-parametric tests will be applied as appropriate.

Further, for physical behavior measures, compositional data analysis (CoDA) will be utilized as appropriate for time-use data [38, 39].

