#### Outcomes

##### Primary outcomes

Difference between intervention and control group in the change from pre- to post-intervention of lower back pain intensity.Difference between intervention and control group in the change from pre- to post-intervention of shoulder/neck pain intensity.

Both primary outcomes will be measured after each working day during 1 week at baseline and 1 week at the end of the intervention, using a 11-point numeric scale (0–10).

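### The primary outcome is a difference in change, the analysis text opens with a comparison after the intervention, and the mixed model does not say how baseline pain enters the contrast

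*Protocol article*

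**What the plan says.** In the protocol article, Primary outcomes lists two contrasts of the same form: "Difference between intervention and control group in the change from pre- to post-intervention of lower back pain intensity" and "Difference between intervention and control group in the change from pre- to post-intervention of shoulder/neck pain intensity". The ratings are "measured after each working day during 1 week at baseline and 1 week at the end of the intervention", so every completer has a baseline score for each pain site.

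Statistical methods opens its account of these outcomes differently: "lower back pain and shoulder/neck pain in the intervention and the control group will be compared after the 16-week intervention". It then plans "mixed-model methods to account for differences between clusters while still providing insight into changes at the individual level" and adds a sentence on the daily ratings: "Mixed-models will also be used to account for repeated measurements of pain intensity and fatigue at the individual level both at baseline and post-intervention".

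The article does not say whether the reported effect is an arm-by-time interaction, an end-of-intervention difference, or an end-of-intervention difference with baseline held equal between arms. Randomization stratifies the units by size only. The model description does not mention that stratum.

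**The concern.** Three contrasts are open for one primary result. In the same participants, the post-only estimate minus the change estimate equals the baseline difference between the arms. With 11 units split 5 and 6, and no stratification on pain, that difference can be sizeable by chance. The researchers are unblinded (Blinding), so the contrast should be fixed in the published text before the results are known.

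The open contrasts also differ in quality. A change analysis is less precise than conditioning on baseline, and it over-corrects a chance imbalance. A literal post-only comparison does not correct the imbalance at all. The trial already collects what is needed to do better than both.

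**Working it through.** **Inputs from the protocol article.** 11 units allocated 1:1 (Abstract). From Sample size: 102 completers per arm, 204 in all; d = 0.39; alpha 5%; power 80%; variance 10.6; effect 1.27 points; 255 recruited with 20% attrition.

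**Assumed, because not given.** Baseline-to-end correlation r of a participant's score, shown for 0.3 to 0.7. ICC, shown for 0 to 0.05. Variance 10.6 is taken as the variance of a participant's score at one time point, the same at both.

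**1. The plan's own figure.** SD = √10.6 = 3.26, and 0.39 × 3.26 = 1.27 points, as stated. Power = Φ(0.39 × √(102/2) − 1.96) = Φ(2.785 − 1.96) = 79.5%, which matches the stated 80%. The calculation uses neither r nor clustering.

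**2. Relative variance of the three contrasts** (individual level, post-only = 1). Power is Φ(2.785/√factor − 1.96).

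| r | post-only: 1 | change: 2(1−r) | baseline-adjusted: 1−r² | power, post / change / adjusted |
|---|---|---|---|---|
| 0.3 | 1.00 | 1.40 | 0.91 | 79.5 / 65.3 / 83.1% |
| 0.5 | 1.00 | 1.00 | 0.75 | 79.5 / 79.5 / 89.5% |
| 0.7 | 1.00 | 0.60 | 0.51 | 79.5 / 94.9 / 97.4% |

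Baseline adjustment saves 9%, 25% and 49% of the variance against post-only. Against change the ratio is (1−r²)/(2(1−r)) = (1+r)/2, a saving of 35%, 25% and 15%. The power figures ignore clustering, as the plan's do, so they show relative gain and not the trial's actual power.

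**3. What the described mixed model gives.** This was simulated with 4,000 data sets, 102 per arm, unit variance, r = 0.5 and no clustering. Standard errors of the arm effect:

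- post-only: 0.140
- change: 0.140
- baseline as covariate: 0.121
- mixed model, separate baseline means per arm: 0.140 (identical to change)
- mixed model, common baseline mean: 0.121

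These agree with √(2/102) = 0.140 and 0.140 × √0.75 = 0.121. One described model therefore covers both the less and the more efficient analysis.

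**4. Chance baseline difference between arms.** Completers per unit m = 204/11 = 18.5. SD of the difference = √(10.6 × [1 + (m−1) × ICC] × [1/(5m) + 1/(6m)]).

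- ICC 0: 0.458, 95% range ±0.90 points
- ICC 0.02: 0.532, ±1.04
- ICC 0.05: 0.627, ±1.23

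**5. How much reaches the estimate.** Given a baseline difference, about +r of it remains in a post-only estimate and about −(1−r) of it enters a change estimate. For the ±0.90 to ±1.23 range:

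| r | post-only | change |
|---|---|---|
| 0.3 | ±0.27 to ±0.37 | ±0.63 to ±0.86 |
| 0.5 | ±0.45 to ±0.61 | ±0.45 to ±0.61 |
| 0.7 | ±0.63 to ±0.86 | ±0.27 to ±0.37 |

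Baseline adjustment removes this component on average.

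**The case against.** The best defence is that the post-only reading is strained. The opening sentence refers back to the primary outcomes, already defined as changes, and its timing phrase may say only when the comparison is made. The same section says the models will "account for repeated measurements of pain intensity and fatigue at the individual level both at baseline and post-intervention", so baseline ratings are in the analysis. An article may also leave the exact contrast, and covariates such as the size stratum, to a fuller plan that is not shown. Much of this stands, and it rules out several stronger readings that a reader might infer.

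- *That baseline is ignored and imbalance left uncorrected.* This is true only of a literal post-only comparison. A change analysis subtracts the imbalance and over-corrects it.
- *That the plan commits to an inefficient analysis.* The described mixed model is compatible with a common baseline mean, which is about as efficient as a covariate.
- *That ±1.2 points is a bias comparable with the 1.27-point target.* It is the raw baseline difference; only the fractions in the last table carry over. Under randomisation all three contrasts have the same expectation. The carry-over is conditional on the imbalance that occurs, and it is the same loss as the extra variance, not an additional one.
- *That the trial would gain 25% or more in precision.* The factors are individual-level. At ICC 0.05 and 18.5 completers per unit, the between-unit part of a unit mean's variance (0.050) is about as large as the within-unit part (0.95/18.5 = 0.051). The gain on the arm contrast also depends on the unit-level correlation, which is unknown.

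The defence does not remove the mismatch between two published sections, and the mixed-model sentence does not settle it.

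**Conclusion.** The point holds as an inconsistency plus an unfixed contrast, not as a validity error. The two sections name different comparisons for the primary outcome, and the mixed model can be fitted so as to reproduce the weaker change analysis.

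At r = 0.5, conditioning on baseline has 0.75 of the individual-level variance of either alternative. It is never less precise in theory at any r, and the gain under clustering may differ. The choice between post-only and change can move the estimate by the baseline difference itself, about ±0.9 to ±1.2 points over the assumed ICC range. The part separating either from a baseline-adjusted estimate is smaller, about ±0.45 to ±0.61 points at r = 0.5.

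These sizes rest on assumed r and ICC, on equal unit sizes, and on the borrowed variance of 10.6. The case for fixing the contrast does not depend on their exact values. This is a nearly free improvement that should be made.

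**What to change.** State one contrast in both Primary outcomes and Statistical methods: the arm difference in end-of-intervention pain, adjusted for baseline, for each pain site.

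- **Preferred.** Keep the planned longitudinal mixed model, with baseline and post-intervention ratings as outcomes, a common baseline mean for both arms, and unit and participant random effects. Allow these effects to differ between the two weeks, so that ratings 16 weeks apart are not forced to be as alike as ratings within one week. This form keeps participants without post-intervention ratings, about 255 − 204 = 51 under the plan's attrition.
- **Alternative.** Model the post-intervention ratings with the participant's baseline mean for the same site as a covariate. This drops participants who have baseline ratings only.

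In either case, include the randomisation size stratum as a fixed effect, and apply the same contrast to fatigue.

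The cost is a few sentences and no new data. The stratum uses a small number of unit-level degrees of freedom: one if there are two strata, but the article does not give the number. With 11 units that cost is small but not nil.

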**Methods:**

The cluster randomized controlled trial is a 16-week workplace organizational intervention implemented through operations managers at the home care units. The operations managers will be introduced to the Goldilocks Work Principle and a GoldiCare tool, to assist the operations managers when composing a “just right” distribution of work schedules throughout the week. The GoldiCare tool provides an overview of the physical strain for each shift, based on the number of patients and their need for care. We expect to include 11 units, which will be randomized to either intervention or control at a 1:1 ratio. Home care workers assigned to the control group will continue to work as normal during the intervention period. Musculoskeletal pain in neck/shoulder and lower back will be the primary outcomes and we will also evaluate the composition of physical behaviors as well as fatigue after work as secondary outcomes. We will collect data using (1) daily questions regarding musculoskeletal pain and fatigue after work, (2) 7 days of objective measurements of physical behavior, (3) questionnaires about the participant’s characteristics, health, and workplace psychosocial stressors and (4) information on the implementation of the GoldiCare tool. In addition, a process evaluation will be conducted using focus group discussions and individual interviews.

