### Trial design

This Goldilocks work intervention will be implemented as a cluster randomized controlled trial with two parallel groups—a no-intervention control arm and an intervention arm, with clusters allocated to the control and the intervention groups in a 1:1 ratio.

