## Methods—participants, interventions, and outcomes

### Study setting

The intervention will be conducted in Trondheim municipality, and an invitation for voluntary participation was distributed to all 13 home care units operating in this area. Eleven positive responses were received. Each home care unit in Trondheim municipality employs 23–95 home care workers providing health services to patients living in their private homes within a defined geographical area. Each unit is organized in teams, which are responsible for a smaller section of the unit, often demarcated by geography. This organizational structure ensures home care workers’ familiarity with the patients, thereby increasing effectiveness, efficiency, and work quality. Seeing familiar home care workers every day also gives structure and reassurance to the patients. The operations manager distributes the daily working lists defining the assignments of each home care worker and an approximate timeframe for the visit to each patient.

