### Sample size

Preliminary mapping of the Trondheim home care sector indicated that 440 home care workers meet the ≥50% employment criteria. As our previous investigation of the home care sector [2] had a 58% participation rate, we expect that 255 home care workers would be recruited for baseline measures if the invitation is distributed to all 440. Assuming a 20% attrition rate, 204 home care workers will complete both baseline and post-intervention measurements, which would result in 102 participants in both the control and intervention arms.

We do not expect different effects in the clusters of intervention and control units since the clusters are made based on feasibility and convenience. With 102 participants in each arm, and an alpha of 5%, we have an 80% chance of detecting an effect size (i.e. an intervention effect) corresponding to a Cohen’s d of 0.39. As no data on the variance in pain scores following a working day in the home care sector currently exist, we were guided by the variance (10.6) from a Goldilocks Work intervention in an industry setting [25], based on which a Cohen’s d of 0.39 would correspond to an intervention effect of 1.27 points. Given that a 1.74 difference on the numeric rating scale between control and intervention is recognized as clinically significant [26, 27] we find that a sample comprising 204 participants is sufficient to detect a clinically meaningful difference.

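### With 11 units, the mixed models as described and the open choice of test can inflate the type I error of the primary pre-to-post comparison

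*Protocol article*

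**What the plan says.** The Outcomes section defines both primary outcomes as the difference between arms in the change in pain from before to after the intervention. Pain is rated after each working day in one baseline week and one final week.

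Statistical methods makes three statements on how this is analysed:

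- On clusters: "We will therefore adjust analyses for the effects of clustering by using mixed-model methods to account for differences between clusters".
- On repeated ratings: "Mixed-models will also be used to account for repeated measurements of pain intensity and fatigue at the individual level both at baseline and post-intervention".
- On the test: "Parametric or non-parametric tests will be applied as appropriate".

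The third statement has no criterion and is not limited to particular outcomes. It directly follows the sentence on pain and fatigue. Compositional analysis of physical behaviour comes in a separate paragraph.

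The number of clusters is small. Abstract, Methods: "We expect to include 11 units, which will be randomized to either intervention or control at a 1:1 ratio". Study setting confirms it: "Eleven positive responses were received". Sample size gives neither an ICC nor a design effect.

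**The concern.** Allocation is by unit, so the information on the treatment effect comes from 11 units. Three routes that the text leaves open can treat it as coming from many more.

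1. **Cancelling intercept.** If baseline and final ratings are both outcomes, a random intercept for the unit is the same in both weeks and drops out of the arm-by-time contrast. What remains is any drift of a whole unit between the two weeks (staffing, season, a change of manager). Unit and participant intercepts do not capture that drift. A model could fit the description in the article and still give the primary effect no protection against clustering.
2. **Reference distribution.** With 9 between-unit degrees of freedom, a normal or person-level reference is too liberal once clustering is appreciable.
3. **Open choice of test.** An ordinary rank test on workers ignores units altogether. Without a rule, the choice can also be made after the data are seen.

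At stake is whether the primary p-values and intervals hold their nominal 5% and 95%.

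**Working it through.** **The plan's own figure.** Sample size states: "we have an 80% chance of detecting an effect size (i.e. an intervention effect) corresponding to a Cohen’s d of 0.39", with 102 per arm and alpha 5% (two-sided assumed). Power = Φ(0.39 × √(102/2) − 1.96) = Φ(2.785 − 1.96) = 79.5%, so the figure reproduces. It does so as a comparison of independent workers with no design effect, and so supplies no variance share for the checks below.

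**Degrees of freedom.** 11 units − 2 arms = 9. The 97.5% point of t on 9 df is 2.262, and 2.262/1.96 = 1.154. If the statistic is truly t on 9 df but is compared with 1.96, the error is 2 × P(t9 > 1.96) = 8.2%.

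**Check A: both weeks as outcomes.** Assumed, with total variance 1: 18 workers per unit (204/11 = 18.5), k = 4 ratings per week, day-to-day variance e = 0.35, participant-by-period variance p = 0 to 0.15, unit-by-period variance u = 0 to 0.02. The participant and unit intercept variances cancel and do not matter.

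- Variance of a worker's change within a unit: c = 2(p + e/4).
- True variance of a unit's mean change: V = 2u + c/18.
- With unit and participant intercepts only, the residual variance pools 6 within-week df and 1 change df per worker: s² = [6e + 2(c + 2u)]/7. The model then uses A = (2s²/4)/18 = s²/36 in place of V.
- With participant-by-period added, it uses B = (c + 2u)/18.
- Type I error = 2[1 − Φ(1.96/√(V/A))], and the same with B.

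Example, p = 0.15 and u = 0.01: c = 2(0.15 + 0.0875) = 0.475; V = 0.02 + 0.0264 = 0.0464; s² = (2.1 + 0.99)/7 = 0.4414; A = 0.01226; V/A = 3.78; 1.96/1.945 = 1.008, giving 31%. With B = 0.495/18 = 0.0275: V/B = 1.687; 1.96/1.299 = 1.509, giving 13%.

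| u | Intercepts only, p = 0 / 0.05 / 0.15 | Plus participant-by-period, p = 0 / 0.05 / 0.15 |
|---|---|---|
| 0 | 5.0 / 10.4 / 18.4% | 5.0 / 5.0 / 5.0% |
| 0.005 | 16.7 / 20.5 / 25.7% | 15.7 / 12.1 / 9.2% |
| 0.01 | 25.8 / 28.1 / 31.4% | 23.7 / 18.2 / 13.1% |
| 0.02 | 37.9 / 38.6 / 39.7% | 33.7 / 27.0 / 19.8% |

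Simulation (4,000 null trials per setting, 5 versus 6 units) agrees within about 2 percentage points. For u = 0.5 to 2% the rounded ranges are about 17 to 39% and about 10 to 34%. A t-test on the unit mean changes with 9 df gave 4.3 to 5.7% throughout.

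**Check B: one value per worker.** This fits a model with the final rating as outcome or with individual change scores. Simulation used 4,000 null trials per setting, 5 versus 6 units and 204 to 205 workers. Ranges run over equal and unequal unit sizes, and the ICC is assumed.

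| ICC | REML, normal | ML, normal | Rank test on workers | REML, t9 | t on unit means | Exact rank test on unit means |
|---|---|---|---|---|---|---|
| 0 | 4.0–4.6% | 4.3–5.0% | 4.8–5.2% | 2.0% | 4.8–5.2% | 2.9–3.1% |
| 0.01 | 5.0–5.1% | 6.0–6.1% | 6.6% | 2.5–2.8% | 4.8–5.1% | 3.1% |
| 0.02 | 5.4–6.2% | 6.4–7.8% | 8.2–9.9% | 2.8–3.3% | 4.6–5.3% | 3.2–3.3% |
| 0.05 | 7.1–8.7% | 9.2–10.9% | 14.8–16.7% | 4.4–5.0% | 4.9–5.5% | 3.3–3.6% |
| 0.10 | 8.1–9.1% | 10.3–12.0% | 23.4–26.5% | 4.8–5.2% | 5.0–5.3% | 3.0% |

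A hand check on tests that ignore units uses the design effect 1 + 17.55 × ICC. At ICC 0.05 it is 1.877, and 2[1 − Φ(1.96/√1.877)] = 15.3%. At 0.10 it is 2.755, giving 23.8%.

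Neither check models the stratification of units by size.

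**The case against.** The strongest reply is that the article names no estimator, degrees of freedom or list of random effects, and that a condensed article may leave these to the full protocol or analysis plan. That stands: silence on Kenward-Roger is not an error. Statistical methods also says that the clustered design calls for special consideration, and its opening sentence compares the arms after the intervention. If baseline enters only as a covariate, the unit intercept does not cancel and check B applies instead of check A.

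Several stronger readings are tempting but not supported:

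- *The trial will use normal-based inference or worker-level rank tests.* The article says neither. The sentence on tests is not expressly tied to the primary outcomes, and non-parametric need not mean ignoring units: the exact rank test on unit means is conservative at about 3%.
- *Mixed-model standard errors are too small in general.* In check B the REML standard error is 0.99 to 1.10 times the empirical one, so the fault there is the reference distribution. ML does run small (0.89 to 0.93 at ICC 0.05 to 0.10), and so do the models in check A.
- *Inflation is certain.* At ICC 0.01 or less, check B with a normal reference gives 4 to 6%.
- *The 18% at zero unit-by-period variance shows the effect of few units.* It comes wholly from omitted participant-by-period variance and falls to 5% once that is modelled.

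What remains is what the text does state. It pairs a mixed-model description, whose plain reading can leave the change contrast unprotected, with an open test choice that does not preserve the unit.

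**Conclusion.** The point holds in conditional form: the described analysis can inflate the primary type I error, and nothing in the article rules that out. The largest risk arises when both weeks are outcomes with unit and participant intercepts only (about 17 to 39%, or about 10 to 34% with participant-by-period added). This assumes unit-by-period variance of 0.5 to 2% of the total and the other shares listed above. With one value per worker, a normal reference costs little at an ICC of 0.01 or less and gives about 7 to 12% at 0.05 to 0.10; a worker-level rank test gives about 15 to 27% at 0.05 to 0.10. The documents supply none of these variance shares, so the ranges show what is possible and do not estimate this trial's error rate. The point should be settled before analysis, because the remedy is wording.

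**What to change.** Replace the quoted sentence on tests with one named primary analysis:

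- a REML mixed model with Kenward-Roger degrees of freedom, or a unit-level t on 9 df, with one of the two chosen in advance;
- random effects for unit-by-period and participant-by-period whenever baseline ratings are outcomes;
- as the only non-parametric alternative, a method that keeps the unit as the unit of inference, such as permuting units over the allocations that the stratified randomisation allowed, with the condition for its use stated beforehand;
- no test that treats workers as independent.

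The cost is wording, plus wider intervals. The reference distribution alone adds about 15% (2.26 against 1.96). Where unit-by-period variance is real, intervals widen further because the standard error then includes it. The stated 80% power allows for neither. No change to recruitment or data collection is needed.
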